#### Predictive validity of the palliative index for mortality (PIM) of the interRAI PC instrument

Based on risk factors, the PIM of the interRAI PC instrument predicts the absolute and relative mortality risk within six months. This index can be used to detect the need for palliative care
[20].

**Psychometrics** Predictive validity is defined as ‘the extent to which a score on a scale or test predicts scores on some criterion measure’
[37].

**Data collection** Caregivers fill out the PIM of the interRAI PC instrument every three months during one year for all residents with palliative care needs as identified through the surprise question.

**Analysis** A survival analysis will be conducted using the Cox proportional hazards regression model. A survival analysis deals with time until the occurrence of a particular event
[38, 39]. In this study, the event of interest is death of the resident. The Cox model is a widely used method for survival analysis in examining time-to-event data
[40]. One of the advantages of the Cox model is that it maintains the variable in its original quantitative form
[40]. Based on previous research on the mortality prediction of the Mimimum Data Set Mortality Risk Index (former PIM), a concordance statistic of 0.75 will be considered as indicative for good predictive value
[20]. Statistical data analysis will be conducted using SPSS.

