The study has two additional research objectives:4)to evaluate the predictive validity of the Palliative Index for Mortality (PIM) of the interRAI PC instrument (The PIM predicts the absolute and relative mortality risk within six months. If predictive validity is judged as high this index can internationally be used to detect the need for palliative care [20]);5)to assess the convergent validity of the CAP ‘Mood’ of the interRAI PC instrument. (This CAP refers to depression, sadness and fear. These are psychological characteristics that regularly occur in persons with palliative care needs. These characteristics contribute to a diminished quality of life of the person and his or her family [21]).

The described study protocol will address the following specific research questions:

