### Validity

Question 3. To what extent is the content of the interRAI PC experienced as complete, accurate and clear according to care professionals in nursing homes? (face validity).

Question 4. Is the Palliative Index for Mortality (PIM) of the interRAI PC instrument a good predictor of the risk of mortality within six months of nursing home residents? (predictive validity).

Question 5. Is the Client Assessment Protocol ‘Mood’ of the interRAI PC instrument a valid screening tool for depressive symptoms in nursing home residents with palliative care needs? (convergent validity).

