#### Phase II: Exploratory trial

**General procedures** The effect of the interRAI PC on the quality of palliative care is evaluated, using a pretest-posttest design with quasi-random assignment to the intervention or control nursing homes. Control nursing homes provide care as usual.

**Setting and participants** Calls for participation are sent out by four umbrella organizations of Flemish nursing homes. An announcement is also made during a national conference for nursing home staff.

Fifteen volunteering nursing homes participate in the study. In the course of one year, these participating nursing homes will fill out the interRAI PC every three months for all residents aged 65 years or older with palliative care needs. The need for palliative care is evaluated by means of the surprise question (‘Would you be surprised if this person was to die within 6 to 12 months?’)
[25, 26]. Based on a list of Flemish nursing homes from the National Institute for Health and Disability Insurance (NIHDI), fifteen care homes which match the intervention nursing homes regarding to facility size, ownership and geographic region are contacted for participation in a control group.

**Intervention** The fifteen experimental nursing homes receive the intervention that is being tested. The intervention consists of 11 steps. The complete intervention is described in Table 
1. The fifteen control nursing homes provide care as usual and therefore do not receive the intervention.

**Sample size** Each year, on average 18 percent of the residents in a nursing home in Flanders, Belgium die
[27]. Based on these data, this study aims at including at least 44 nursing home residents with palliative care needs, in order to detect an effect of the use of the interRAI PC instrument on the identified factors. Calculations are based on a medium effect size of 0.50, a two-sided significance level of 0.05 and a power of 0.90 (using G*Power 3.1.5 software)
[28].

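### The PIM is scored only in residents already flagged by the surprise question, so the study cannot answer Question 4 for residents in general or support using the PIM to detect palliative care need

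*Protocol article*

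**What the plan says.** Four statements in the Protocol article bear on this point.

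- **Who is scored.** The section on predictive validity of the PIM collects the index every three months "for all residents with palliative care needs as identified through the surprise question". The sections Design of the complex intervention and Phase II: Exploratory trial limit the whole instrument to the same group, aged 65 or older.
- **How need is defined.** Under Phase II, Setting and participants: "The need for palliative care is evaluated by means of the surprise question". Staff are asked: "Would you be surprised if this person was to die within 6 to 12 months".
- **What is asked.** Question 4, under Validity, asks whether the PIM is "a good predictor of the risk of mortality within six months of nursing home residents". It carries no restriction to residents with palliative care needs. Question 5, directly below it, does.
- **What would follow.** Additional objective 4 in the Background states: "If predictive validity is judged as high this index can internationally be used to detect the need for palliative care". The yardstick, in the Analysis paragraph of the PIM section, is that "a concordance statistic of 0.75 will be considered as indicative for good predictive value". It is attributed to earlier research on the predecessor index, whose study population is not described.

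The limitations in the Discussion do not mention that PIM validation is confined to flagged residents.

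**The concern.** The sample is selected on a staff judgement of expected death, which is close to what the PIM predicts, and that same judgement serves as the study's marker of need. Residents whom staff did not flag, including any who die unexpectedly, have no PIM score. Those residents are where a detection tool would either add something or raise false alarms.

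The final report could therefore answer a broader question than the one studied. A good concordance among flagged residents could be read, as the Background invites, as support for screening whole nursing home populations with the PIM. A modest concordance could be read as a failure of the index when part of the shortfall might come from preselection. The first risk follows directly from the text. The second depends on facts the article does not give.

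**Working it through.** **Part 1. What the design can estimate (no arithmetic needed).**

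Cross-classify all residents by surprise question (flagged or not) and by PIM (above or below some threshold). The study fills only the flagged row.

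1. *Reference standard = need as the study defines it (flagged).* Specificity is P(PIM low | not flagged), and its denominator in the sample is zero. The share of flagged residents above a threshold can be computed, but without the unflagged row it says nothing about telling residents with need from those without.
2. *Reference standard = death within six months among all residents.* Sensitivity needs all deaths and specificity needs all survivors. Unflagged deaths and unflagged survivors are both unscored, so neither can be estimated.
3. *What remains.* Concordance within the flagged row, which is risk ranking among residents already identified. This is a legitimate result, but it is neither Question 4 as worded nor the inference in objective 4.

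**Part 2. What preselection could do to the concordance (illustration).**

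The plan's 0.75 comes from a cited source, so nothing in the article allows it to be reproduced.

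From the document: 18% of residents die per year (Sample size paragraph). At a constant rate, six-month mortality is 1 − 0.82^0.5 = 0.094, about 9%.

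Assumed, not in the document: the index has concordance 0.75 in all residents; 20% to 40% are flagged; the correlation ρ between the PIM and the latent judgement behind the surprise question is 0.3, 0.5 or 0.7; that judgement either adds prognostic information beyond the PIM or does not; six-month mortality of 15% as an alternative.

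Model:
- PIM score X ~ N(0,1); judgement S = ρX + √(1 − ρ²)·U, with U ~ N(0,1) independent of X.
- logit P(death within six months) = a + bX + gU, with g = 0 (nothing added) or g = 0.5 (information added).
- a is set to give the mortality and b to give an area under the ROC curve (AUC) of 0.75 in all residents. The AUC is then recomputed in the top 20%, 30% and 40% on S. The AUC at six months stands in for the Cox concordance.

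AUC among flagged residents, over both mortality levels and all three fractions:

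| ρ | nothing added | information added |
|---|---|---|
| 0.3 | 0.74 | 0.72–0.73 |
| 0.5 | 0.72–0.73 | 0.69–0.70 |
| 0.7 | 0.70–0.71 | 0.65–0.67 |

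Two variants mark out the range:
- Judgement as prognostic as the PIM itself, ρ from 0.4 to 0.7: 0.66 to 0.71.
- Weak relation, nothing added: about 0.746 to 0.749 at ρ = 0.2, and no loss as ρ approaches 0.

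The result therefore runs from about 0.65 to essentially 0.75, and assumptions that the article does not supply decide where in that range it falls.

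**The case against.** The strongest defence is that the population is openly stated. The Discussion describes validity research among residents with palliative care needs and a final product for that group. The instrument is intended for people near the end of life, so studying its mortality index there is coherent. Because the surprise question looks 6 to 12 months ahead and the PIM six months, ranking risk among flagged residents remains a useful question. The sentence in the PIM section, "This index can be used to detect the need for palliative care", is cited background, and this is an additional objective of an exploratory study.

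All of that stands as a defence of the sample. It does not rescue the inference in objective 4, which makes this study's own result the condition for a detection use. Nor does the general wording in the Discussion withdraw that inference.

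A reader might go further and infer that 0.75 is an unfair pass mark that a good index is bound to miss, and that it should be dropped. The documents do not support this, for three reasons:
- The population behind 0.75 is not described. If it was similarly selected, there is no bias against the benchmark.
- The figure is worded as indicative, and no test or go/no-go decision is attached to it.
- The predicted shortfall comes from assumed inputs and shrinks to nothing when the surprise question is weakly related to the PIM. A loss of 0.01 to 0.02 would also be small beside sampling error: at an observed 0.75 with an assumed 300 residents and 90 deaths, the approximate 95% interval is 0.69 to 0.81.

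The absence of a stated confidence interval is not counted against the article, since that is detail left to a fuller plan.

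**Conclusion.** The point holds for the scope of the claim. The PIM is evaluated only in residents whom the study has already identified as needing palliative care. The data can show risk ranking within that group. They cannot answer Question 4 for nursing home residents in general, and no concordance, however high, can support using the PIM to detect need. This rests on the text alone and needs no simulation.

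On the benchmark, the conclusion is only conditional. If 0.75 came from a less selected population, preselection on expected death may lower the concordance here, to between about 0.65 and nearly 0.75 under the assumed correlations and flagged fractions. That justifies a caveat beside the reference value, not its removal.

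**What to change.** 1. Reword Question 4, and the conclusion drawn from it, as prediction of death within six months among residents aged 65 or older who are positive on the surprise question.
2. In additional objective 4, remove the inference from high predictive validity to detection of need, or state that this study does not test it.
3. Add to the limitations in the Discussion that unflagged residents are not scored, so performance of the PIM as a detection tool is not assessed.
4. Keep 0.75 as an indicative reference. Add that if it was obtained in a less selected population, a lower value here may partly reflect preselection.

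The cost is wording and a narrower claim; no new data are needed. If the sponsor wishes to keep the detection claim, the PIM and six-month vital status would also be needed in at least a random sample of unflagged residents, which is a real extension of data collection.

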#### Convergent validity of the client assessment protocol ‘Mood’ (CAP ‘Mood’)

The CAP ‘Mood’ of the interRAI PC instrument refers to depression, sadness and fear. These are psychological characteristics that regularly occur in persons with palliative care needs. These characteristics contribute to a diminished quality of life of the person and his or her family
[21].

**Psychometrics** Convergent validity is a subtype of construct validity and is defined as the degree to which two measures of constructs that theoretically should be related, are in fact related
[41].

### Data collection

The CAP Mood is tested against a ‘gold standard’ in order to answer the second research question. The Cornell Scale for Depression in Dementia (CSDD) is used as the ‘gold standard’. Together with the completion of the interRAI PC instrument, an independent assessor also completes the CSDD every three months during one year for all residents with palliative care needs. The CSDD is a 19-item scale, designed for the screening of depressive symptoms in older adults with and without dementia. The CSDD is the only depression scale that has been validated for both populations
[42, 43]. Research shows that the instrument is equally valid in populations with or without dementia
[44]. In prior research, the CSDD already has been used as a ‘gold standard’
[45].

**Analysis** The level of agreement between the CAP Mood and the CSDD test scores will be explored using comparisons of means, agreement coefficients and diagnostic accuracy. A CSDD cut-off of 8 will be used as ‘gold standard’. Probability levels of 0.05 will be considered significant
[45]. Statistical data analysis will be conducted using SPSS.

### Ethics statement

Approval to conduct this research was granted by the Belgian Commission for the Protection of Privacy (BCPP) and the UZ Leuven Medical Ethics Committee (file number B322201421986).

All nursing home residents with palliative care needs or their representatives are asked to sign an informed consent agreement. Refusing to participate will not affect the care services offered to the resident. When residents or their representatives decide to participate, they can withdraw their consent at any time.

A formal procedure was undertaken to enable caregivers to fill out the interRAI PC on a secured online web-application (belrai.org).

## Discussion

This article describes the research protocol of a mixed methods study with a longitudinal, quasi-experimental pretest-posttest design. The study is based on phases 0, I and II of the Medical Research Council (MRC) Framework
[22, 23]. The main aims of the study are to evaluate (1) the effect of the interRAI PC on the quality of palliative care in nursing homes; (2) the feasibility of the interRAI PC; (3) the face validity of the interRAI PC; (4) the predictive validity of the Palliative Index for Mortality (PIM) of the interRAI PC; (5) and the convergent validity of the CAP ‘Mood’ of the interRAI PC.

Previous research has shown a need for well-validated CGAs in clinical practice to evaluate an older person’s medical, psychosocial and functional condition
[46]. Based on a systematic review, the authors found the interRAI PC to be the most comprehensive geriatric assessment for palliative care in nursing homes. However, insufficient data are available on the validity and the effectiveness of the instrument in a nursing home population
[19]. Therefore, this research is conducted on the effect, the feasibility and the validity of the interRAI PC instrument in a population of nursing home residents with palliative care needs.

The interRAI PC consists of various components and the introduction of the interRAI PC in clinical practice requires several steps at different stages
[47]. Interventions ‘comprising a number of separate elements which seem essential to the proper functioning of the interventions although the ‘active ingredient’ of the intervention that is effective is difficult to specify’ are considered as complex interventions
[48]. For trials of such complex interventions, Campbell et al. recommended the MRC framework
[22, 23].

The phased MRC approach, which combines qualitative and quantitative methods, improves the study design and implementation and will contribute to a higher generalizability of the results
[23]. A supplementary strength of the study lies in the fact that it is longitudinal. Several observations of the same variables will be conducted over a period of time. In addition, changes, developments and learning processes over time can be detected. Because of the pretest-posttest design and the use of a control group, expected improvements in the quality of palliative care can be examined.

Limitations of the study also need to be acknowledged. Because of time restrictions, the interRAI PC instrument will only be filled out during one year. Therefore, the maximum amount of longitudinal measures is limited to four. Furthermore, the experimental group consists of all nursing home residents with palliative care needs of fifteen nursing homes (public, private, profit and private commercial nursing homes). However, this sample might not be representative of the general Flemish nursing home population. Additionally, due to ethical and practical constraints, participants will not be randomly assigned to the intervention or control group. Because of the strong commitment requirements, nursing homes which volunteer in the experimental group are all included. Moreover, it is impossible to refuse caregivers to fill out the interRAI PC since the instrument is made accessible through the online webapplication BelRAI. Nursing homes are thus included in the experimental group if they are interested in filling out the interRAI PC.

The final result of the study will be a psychometrically evaluated CGA for nursing home residents with palliative care needs, with outcomes that can be used for care planning. If the validity and the effect of the use of the interRAI PC instrument are evaluated positive, this study protocol can form the basis for a larger-scale phase III randomized controlled trial and a broader implementation of the interRAI PC in nursing homes (phase IV). This can further enhance and stimulate optimal palliative care for nursing home residents and eventually also for adults living in other settings. Finally, the international relevance of this study protocol needs to be acknowledged. While the interRAI suite of instruments -and more specifically the interRAI PC instrument- is tested and implemented worldwide, this study protocol can provide guidelines to evaluate the effect, the validity and the usability of interRAI PC in other countries.

## Abbreviations

CGAs: Comprehensive geriatric assessments
interRAI PC: interRAI palliative care instrument
CAPs: Client assessment protocols
MRC: Medical research council
PIM: Palliative index for mortality
QIs: Quality indicators
AGDHA: Australian government department of health and ageing
NIHDI: National institute for health and disability insurance
POS: Palliative care outcome scale
RI: Retrospective information
ANCOVA: Analysis of covariance
CSDD: Cornell scale for depression in dementia
BCPP: Belgian commission for the protection of privacy.
